## **3.4 Data Management**

### **3.4.1 Data Quality Control**

Qualified research assistants will be trained in collecting data by conducting pre-tests of the questionnaires and other data collection tools. The PI will cross-check all data entry forms to ensure errors are corrected. All data will be entered in duplicate to reduce data entry errors. Hard copies of data will be stored under lock and key. Soft copies of data will be stored in a One drive account accessible to the principal investigator only.

### **3.4.2 Data Analysis**

Data will be analyzed using STATA 16. Summaries of variables will be obtained using frequencies, means and standard deviations. Histograms, bar graphs and box and whisker plots will be used to check for skewness and identify outliers. Proportions and frequencies will be used to summarise all binary or categorical variables. Means and standard deviations will be used to summarise continuous variables and proportions and frequencies for categorical variables. Chi-square tests will be used to determine associations between categorical variables. Independent sample t-tests or one-way ANOVA will be used to test for differences in means, and a z-test used to assess the difference in proportions. Simple and multiple logistic regression analysis will be carried out between outcome variables (binary) and other variables identified as potential confounders to test for the magnitude and strengths of associations. All tests will be two-tailed and statistical significance set at 0.05.

[figure not shown]

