## **1.10 Study hypothesis**

The hypotheses that will be tested in the study are as follows:

1. There is no difference in the proportion of adolescent ART visits that had BPs checked between facilities exposed to the intervention and unexposed facilities.
2. There is no change in arterial stiffness parameters of hypertensive adolescents living with HIV after six months of exposure to the TPB- based intervention.

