### **3.3.4 Recruitment**

Recruitment into the study will be done at three levels: health facilities, health workers and adolescents living with HIV.

1. **Health facility recruitment**

The PI will invite potential participating clusters (i.e. health facilities) through their respective administrators to participate. In each consenting facility, the PI will identify a primary contact person for the research team.

1. **Clinical staff recruitment**

Once facilities are recruited, the PI will contact the focal persons to obtain details of potential clinical staff who may be interested in participation based on the inclusion and exclusion criteria. The potential participants will be engaged to discuss the study protocol. Those who express interest will be provided with a study invitation pack, including a letter of invitation, information sheet and consent form.

1. **Patient recruitment**

Using a random sequence provided by the study team, a random sample of 20 adolescents living with HIV per facility will be selected for baseline and end-line assessment. The consent of their caregivers will be sought, followed by the adolescents’ consent or assent as may be age-appropriate.

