### **3.3.6 Randomization**

**a. Sequence generation:** The unit of randomization will be the health facility. Randomization will be performed by a statistician independent of the study team, using computer-generated random permuted blocks and will be stratified by type of health facility (regional, district/ municipal, Polyclinic, Health Centre). Twelve facilities will be in the intervention arm and the rest in the control arm. The study statistician will provide each facility with a computer-generated list of random numbers to select a sample of 20 adolescent clients to participate in the baseline and end-line survey.

**b. Allocation concealment**: Each facility will eventually become aware of its allocation, but allocation will be concealed until the baseline assessment is completed. Adolescents will not be allocated to alternative interventions within a facility, so allocation concealment will not be an issue.

**c. Implementation of clusters:** The PI will provide the list of prospective facilities by type to the study statistician, anonymized by an ID**.** The study statistician will generate the random sequence and allocate practices to two separate dummy-coded groups without knowing which group will receive the intervention; the study statistician will remain blind to allocation until the collected follow-up data. Random allocation of clusters to intervention or control will occur consecutively as practices are recruited until the target sample size (24) is reached.

**d. Blinding:** Given the nature of the intervention, healthcare workers will inevitably be aware of their allocation and thus, blinding participants will not be possible. Each facility will also become aware of allocation. However, facilities will not be informed of allocation until after both facilities and individual health workers are identified and recruited (i.e., not until after baseline assessment). Adolescents within each facility will remain blind to allocation. The outcome assessors will be kept blind to the allocation. The facility contact that will use the random sequence of numbers to identify the sample of 20 patients within each facility will possibly not be blind to allocation. Blinding the entire research team is also impossible as intervention facilities will be contacted to arrange the sessions. However, the study statistician conducting the outcome analysis will remain blinded to allocation until after the outcome data have been collected at follow-up.

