**Table 1** **Application of Theory of Planned behavior to intervention design and measurement**

| **TPB Constructs** | **Intervention package** | **Process Measures** |
| --- | --- | --- |
| Attitude | 1. Orientation on hypertension risk among adolescents living with HIV | Pre and post-test scores |
| Subjective norms | 1. Audit and feedback 2. Opinion leaders 3. Patient education 4. Reminders(posters) | 1. The proportion of planned feedback sessions undertaken 2. The proportion of planned engagement sessions with opinion leaders held 3. The proportion of planned patient education sessions held 4. The proportion of expected posters pasted |
| Perceived behavioral control | 1. Provision of a paediatric sphygmomanometer 2. Orientation on BP measurement technique 3. Provision of clinical decision support | 1. The proportion of intervention facilities with paediatric sphygmomanometer 2. a.Proportion of target staff oriented on BP measurement technique   b. change in accuracy of BP measurements post-orientation   1. The proportion of intervention facilities with clinical decision support pack |

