## **3.6.4 Compensation**

Adolescent participants coming for follow up assessments outside their scheduled facility visits will have their transportation reimbursed.

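### Section 3.4.2 names only independent-sample tests for means, without stating the contrast, although CAVI and BP appear to be measured twice in the same adolescents

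*Protocol*

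**What the plan says.** Section 3.4.2 (Data Analysis) fixes the method for means: "Independent sample t-tests or one-way ANOVA will be used to test for differences in means". The only regression it names is logistic, for binary outcomes. The same section adds: "All tests will be two-tailed and statistical significance set at 0.05". It names no paired, change-score or baseline-adjusted method for a continuous outcome, and it does not say which two sets of means are to be compared.

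The measurement plan points to one cohort seen twice:

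- Section 3.3.4: "a random sample of 20 adolescents living with HIV per facility will be selected for baseline and end-line assessment".
- Section 3.3.6 has each facility use one random list "to select a sample of 20 adolescent clients to participate in the baseline and end-line survey".
- Section 3.3.5 enrols about 480 adolescents in total, and the budget table pays travel for 480 adolescents at a frequency of 2.
- Section 3.6.4 expects returning participants: "Adolescent participants coming for follow up assessments outside their scheduled facility visits will have their transportation reimbursed".

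Section 3.3.9 b schedules office BP, ambulatory BP and CAVI at baseline and six months in both arms. Hypothesis 2 in section 1.10 is worded as a change: "There is no change in arterial stiffness parameters of hypertensive adolescents living with HIV after six months of exposure". Objective 3 in section 1.9 and the two-arm design in section 3.3.1 imply a comparison between arms.

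**The concern.** Two measurements on one adolescent are correlated. The named tests treat the two groups of values they compare as coming from different people. What follows depends on a contrast that the protocol leaves open.

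- **Baseline against six months.** The independent test uses a standard error that is too large, so its interval is too wide. A real change in arterial stiffness could be reported as no change.
- **Arm against arm at six months.** The groups really are different adolescents, so the independence assumption is not broken by pairing. The cost is that each adolescent's own baseline, collected at some effort (24-hour monitoring, a CAVI session), plays no part.

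Objective 3 rests on these measures. In the hypertensive subgroup, where numbers will be small, precision matters most.

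**Working it through.** **Inputs.** Two-sided alpha of 0.05, critical value 1.96 (section 3.4.2). Twelve facilities of 20 adolescents per arm, so 240 per arm (section 3.3.5). ICC 0.05 (section 3.3.5), stated for the primary outcome and assumed here for CAVI and BP. The correlation ρ between an adolescent's baseline and six-month values is not in the protocol; 0.3 to 0.7 is assumed.

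**The plan's own figure.** The protocol gives no power figure for CAVI or BP. Its primary-outcome size does reproduce: 17% against 34% needs 103 per arm; the design effect is 1 + 19 × 0.05 = 1.95; 103 × 1.95 = 200.85; divided by 20, that is 10.04 facilities per arm, against the stated 10.

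**Before-after use of the independent test.** With equal SDs the test uses σ√(2/n), while the true standard error is σ√(2(1−ρ)/n). Write f = √(1−ρ).

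- True alpha = 2[1 − Φ(1.96/f)].
- At a change that the paired test detects with 80% power (2.80 true standard errors), power = Φ(2.80 − 1.96/f).

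| ρ | 1.96/f | true alpha | power (paired test: 80%) |
|---|---|---|---|
| 0.3 | 2.34 | 0.019 | 68% |
| 0.5 | 2.77 | 0.0056 | 51% |
| 0.7 | 3.58 | 0.0004 | 22% |

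Simulation (5,000 runs, 12 facilities of 20) gives alpha 0.018, 0.004 and 0.0002 at ICC 0.05 with fully persistent facility effects. For hypertensive adolescents only, the 10.5% prevalence cited in section 2.5.4 gives 240 × 0.105 ≈ 25 in the intervention arm. Simulating 25 independent pairs gives alpha 2.0%, 0.7% and 0.1%, and power 70%, 54% and 25%.

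These alphas depend on stable facility effects. If only half of the facility variance persists over six months, the simulated alpha of the same test is 0.072, 0.046 and 0.027.

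**Between-arm use at six months.** Pairing has no effect on alpha: simulated values are 0.049 to 0.052 at ICC 0. Adjusting for own baseline multiplies the variance by 1 − ρ² if facility means persist with the same ρ. Where the adjusted analysis has 80% power, the end-line-only analysis has Φ(2.80√(1−ρ²) − 1.96), with facility handled in both:

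- ρ = 0.3: 76%
- ρ = 0.5: 68%
- ρ = 0.7: 52%

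**If facility means do not persist.** In SD² units, the variance of a facility mean is 0.05 + 0.95/20 = 0.05 + 0.0475 = 0.0975. Take ρ = 0.5 for individuals and no facility persistence. Adjusting for own baseline leaves 0.05 × 1.25 + 0.0475 × 0.75 = 0.098. The gain has vanished.

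**Whether a paired t-test would do.** With half of the facility variance persisting, a plain paired before-after t-test has simulated alpha 0.14, 0.16 and 0.22 for ρ of 0.3, 0.5 and 0.7. A between-arm t-test on facility-mean changes stays at about 5%.

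**The case against.** Several points on the other side have force.

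- **Alpha.** A reader might infer that the stiffness and BP tests in general run far below 5%. The documents do not support that. It applies only to the before-after use with stable facility effects. Between arms, pairing leaves alpha at about 5%, and ignoring facility raises it: 2[1 − Φ(1.96/√1.95)] = 0.16 if the ICC of 0.05 applies.
- **Change scores.** A reader might also infer that an independent t-test cannot use the baseline at all. It can, if applied between arms to six-month changes. Section 3.4.2 does not rule this out, but it does not specify it either. The relative variance of a change score is 2(1−ρ), which is larger than the 1 − ρ² of baseline adjustment.
- **Pairing is not stated beyond doubt.** Section 3.3.9 b speaks of a cross-sectional survey and of randomly selected adolescents at each time, and the travel budget would fit two fresh samples. Even so, two fresh samples could reach 960 adolescents, while section 3.3.5 enrols about 480, and sections 3.3.4 and 3.3.6 describe one sample for both rounds.
- **Categorical use.** Section 3.3.9 also classifies CAVI by cut-offs and BP by category. For those binary versions section 3.4.2 offers logistic regression, and the figures above do not carry over. They concern continuous values only.
- **Health workers' scores.** It is tempting to extend the point to "Pre and post-test scores" in Table 1. Those are process measures, and no test on them is specified, so the extension would be conjecture.
- **Left to an SAP.** Baseline adjustment often is. Here, however, the protocol does name the tests for means, and the ones it names do not suit the change described in hypothesis 2.

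**Conclusion.** The point holds as a mismatch between the measurement plan and the named tests, together with an unstated contrast. For a before-after comparison, the independent test has true alpha of about 2% to below 0.1% and power of 68% to 22% against 80%, assuming ρ of 0.3 to 0.7 and stable facility effects. For the randomised comparison the loss is efficiency only: 76% to 52% power against 80%. That assumes facility means persist as individual values do, and it shrinks to almost nothing if they do not.

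All of this rests on the same adolescents being seen twice, which is the best reading of the protocol, and on correlations it does not give. These are secondary outcomes with no stated power. The case for acting is that the correction is nearly free and settles which comparison the named tests are meant to make.

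**What to change.** In section 3.4.2, state that the contrast for continuous CAVI, office BP and ambulatory BP is between arms at six months. Analyse the six-month value by regression on arm and the adolescent's own baseline value of the same measure, optionally with the facility's baseline mean as well, in a model that accounts for facility. Report within-arm change descriptively, with an interval that respects both pairing and facility clustering. Do not simply substitute a paired t-test.

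The cost is a change of wording. No new participants or measurements are needed, since both rounds are already planned and section 3.6.2 assigns study codes. The two rounds must be linked by those codes, and a simple rule is needed for missing baselines, such as mean imputation of the baseline covariate.

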### **3.3.5 Sample size**

This study is designed to detect a doubling (100%) of the proportion of adolescent visits that had BP screening done (conservatively calculated in STATA version 16 as an increase from 17% to 34%) between the intervention and control groups. It is based on the assumption of a 2-sided test with 80% power at a 5% significant level, cluster sizes of 20 adolescents and an intra-cluster correlation coefficient (ICC) of 0.05. Accordingly, two groups of ten (10) health facilities will be needed at the minimum. As this sample size estimation does not account for any potential loss to follow-up, we will recruit additional two facilities per arm (24 in total). Thus, a total of about 96 health workers (4 per facility) and about 480 adolescents living with HIV (20 per facility) will be enrolled in this study.

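### Facilities are randomised and the sample size allows for clustering, but the named tests ignore it: at the protocol's own ICC a nominal 5% test has about a 16% false-positive rate

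*Protocol*

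**What the plan says.** Protocol section 3.3.1 describes a two-arm cluster-randomised study, and section 3.3.6 confirms it: "The unit of randomization will be the health facility". Section 3.3.5 plans for this. It assumes "cluster sizes of 20 adolescents and an intra-cluster correlation coefficient (ICC) of 0.05", with "a 2-sided test with 80% power at a 5% significant level" and an effect "conservatively calculated in STATA version 16 as an increase from 17% to 34" percent. It concludes that "two groups of ten (10) health facilities will be needed at the minimum", and to cover losses adds that "we will recruit additional two facilities per arm (24 in total").

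Section 3.4.2 names the tests for the trial. For continuous and binary outcomes it says "Independent sample t-tests or one-way ANOVA will be used to test for differences in means, and a z-test used" for comparing proportions. It adds chi-square tests for categorical variables, and for regression: "Simple and multiple logistic regression analysis will be carried out between outcome variables (binary) and other variables identified as potential confounders". All tests are two-tailed at 0.05. The section mentions no facility random effect, generalised estimating equations, cluster-robust variance or facility-level summaries, and neither does any other part of the protocol.

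**The concern.** In their usual form, the z-test, chi-square test, t-test, one-way ANOVA and logistic regression all take observations as independent. Adolescents in one facility are seen by the same staff, and the intervention acts on those staff, so their outcomes will tend to be alike. Section 3.3.5 assumes as much by using a positive ICC.

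The first hypothesis in section 1.10 compares the proportion of visits with a BP check between exposed and unexposed facilities, and section 3.3.9 takes one visit from each of 20 adolescents per facility. The z-test for proportions is the natural reading of how that comparison will be made. If it is run on about 480 adolescents as independent units, p-values will be too small and intervals too narrow. A significant primary result could not be taken at face value.

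**Working it through.** **Inputs.** From section 3.3.5: rates p1 = 0.17 and p2 = 0.34, two-sided α = 0.05, power 80%, m = 20 per facility, ICC = 0.05, at least 10 facilities per arm, 12 per arm recruited. From section 3.3.6: 12 facilities against 12, stratified by four facility types.

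**Reproducing the plan's own figure.**
- Individually randomised n per arm = [1.960 × √(2 × 0.255 × 0.745) + 0.842 × √(0.17 × 0.83 + 0.34 × 0.66)]² / 0.17² = 102.003, rounded up to 103.
- Design effect = 1 + (20 − 1) × 0.05 = 1.95.
- 103 × 1.95 = 200.85 per arm, and 200.85 / 20 = 10.04 facilities. With exactly 10 facilities per arm the power is 80.2%, so the stated 10 is reproduced.
- Without the design effect the answer would be 103 / 20 = 5.15 facilities. The stated number is reached only by allowing for clustering.

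**Effect of ignoring clustering in the test.** The true variance of the difference is 1.95 times the variance that the z-test uses. The standard error is therefore understated by √1.95 = 1.40.
- Actual type I error = 2 × [1 − Φ(1.960 / √1.95)] = 2 × [1 − Φ(1.404)] = 0.160.
- Coverage of a nominal 95% interval = 1 − 0.160 = 84%.
- Effective sample size = 480 / 1.95 = 246.

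**Sensitivity to the ICC, with m = 20.**

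| ICC | Design effect | Actual type I error |
| --- | --- | --- |
| 0.01 | 1.19 | 7.2% |
| 0.02 | 1.38 | 9.5% |
| 0.05 (protocol) | 1.95 | 16.0% |
| 0.10 | 2.90 | 25.0% |
| 0.15 | 3.85 | 31.8% |

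**Simulation.** Beta-binomial data with no effect, ICC 0.05, 20 per facility, 10 or 12 facilities per arm, a common rate of 17% or 25.5%, and 200,000 trials per setting. The z-test that ignores facility rejected in 16.1% to 16.2% of trials. A t-test on the facility proportions rejected in 5.0%.

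**Power of the facility-level test.** The standard error is √[(0.1411 + 0.2244) × 1.95 / (20k)] for k facilities per arm, with a noncentral t reference.
- k = 12, 22 df: SE 0.0545, noncentrality 0.17 / 0.0545 = 3.12, power 85%.
- k = 12 with the four strata as fixed effects, 24 − 2 − 3 = 19 df: power 84%, keeping the same standard error.
- k = 10, 18 df: SE 0.0597, noncentrality 2.85, power 77%.

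**The case against.** Several points can fairly be made for the protocol.

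- **The list is generic.** Section 3.4.2 does not tie a test to the primary comparison or state the unit of analysis. An independent t-test could be run on facility proportions, and the protocol never calls its logistic regression ordinary. But a z-test for a difference in proportions most naturally means individual-level data, and no sentence points to facility summaries.
- **A statistical analysis plan may exist.** Random effects, degrees of freedom and small-sample corrections are commonly left to it, and section 3.3.1 commits to the CONSORT guidance for cluster trials. That would answer a protocol that was silent. This one names tests that do not fit its design, and a later plan that adjusted for clustering would contradict section 3.4.2. The CONSORT reference specifies no analysis.
- **The 16% is conditional.** It rests on a planning ICC for which section 3.3.5 gives no source. This stands, and a smaller ICC gives less inflation.
- **It does not carry over to every outcome.** This also stands. The protocol gives no ICC for blood pressure or the cardio-ankle vascular index (CAVI). Section 1.10 limits the arterial-stiffness hypothesis to hypertensive adolescents. If the 10.5% prevalence cited in section 2.5.4 applied, about 2 of 20 per facility would qualify. The design effect would then be roughly 1.05 to 1.10, and the type I error about 6% (5.6% to 6.2%) at ICC 0.05. The same applies to the investigation and management components of the primary outcome, which arise only when BP is raised.

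**Conclusion.** The concern holds. The protocol's design and sample size allow for clustering, and its stated analysis does not. For the BP-check proportion, the outcome on which the trial is sized, the nominal 5% test has an actual two-sided error of about 16% and the 95% interval covers about 84%. Both figures assume ICC 0.05, 20 adolescents per facility and a test run on individuals without a facility term. The direction does not depend on the ICC: any positive value takes the error above 5%. Outcomes restricted to adolescents with raised BP would show less inflation, and no figure can be given for BP or CAVI across all participants without an ICC for them. Because the validity of the primary conclusion is affected, this should be corrected before the analysis.

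**What to change.** Rewrite the between-arm comparisons in section 3.4.2 so that each accounts for facility.

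- **Binary outcomes:** either a t-test or regression on the 24 facility proportions, or a mixed-effects logistic model with a facility random intercept and a small-sample correction.
- **BP and CAVI:** a linear mixed model with a facility random intercept and Kenward-Roger degrees of freedom.
- **Stratification:** carry the facility-type strata from section 3.3.6 into the analysis. A facility-level regression then has about 19 degrees of freedom instead of 22.
- **Reporting:** give the arm difference with a cluster-adjusted 95% interval and the observed ICC. Keep the z-test, chi-square and individual-level t-tests for description only.

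The cost is wording. No extra facilities, adolescents or data are needed, because the data extraction form already records the facility. Intervals will be wider than the named tests would give, but that is the width the sample size already assumed. Power stays near 85% with 12 facilities per arm (about 84% with strata). It falls to 77% if only the stated minimum of 10 per arm is retained, so the two additional facilities per arm matter.

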### **3.3.9 Outcomes**

#### **a. Primary outcomes**

The primary outcome will be the effect of the intervention on healthcare workers’ adherence to the guideline. It will assess adherence to recommendations on the

1. frequency of screening
2. Detection of elevated or high BP,
3. Investigation of high BP and
4. Management of elevated or high BP.

These will be assessed using a data extraction tool based on the HIV client care booklet. The tool will extract the data from the client care records of adolescents who received care within the period of interest. At baseline, it will assess the records of 20 randomly selected adolescents who received care at the facility six months prior to the assessment and extract the data from their most recent visit. At follow up, data will be extracted from the most recent visit of 20 randomly selected adolescents who received care at the facility after the intervention commenced.

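### Section 3.4.2 names neither the baseline facility blood-pressure-check rate nor the stratification factor as a term in the treatment comparison

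*Protocol*

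**What the plan says.** **Baseline outcome.** Section 3.3.9 (a) measures adherence from client records twice. Of the first measurement it says: "At baseline, it will assess the records of 20 randomly selected adolescents who received care at the facility six months prior to the assessment". A further 20 adolescents' records per facility are taken at follow-up. Every facility therefore has its own pre-intervention blood pressure (BP) check rate.

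**Stratification.** Section 3.3.6 (a) says that randomisation "will be stratified by type of health facility (regional, district/ municipal, Polyclinic, Health Centre"), using permuted blocks of unstated size, with twelve facilities in the intervention arm and the rest in control.

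**Timing of allocation.** Section 3.3.6 (c) has the investigator supply a list of facilities by type, and then says: "Random allocation of clusters to intervention or control will occur consecutively as practices are recruited until the target sample size (24) is reached". Section 3.3.6 (b) withholds allocation from facilities until the baseline assessment is finished.

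**Analysis.** Section 3.4.2 lists chi-square tests, t-tests or one-way ANOVA for means, and a z-test for proportions. It adds simple and multiple logistic regression on "other variables identified as potential confounders to test for the magnitude and strengths of associations". No covariate is named, and there is no rule for identifying one.

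**The concern.** In a trial of 24 clusters, two covariates have a reason in the design to be in the treatment model. One is the facility's own earlier performance on the outcome. The other is the factor used to stratify the randomisation. Both will be on file for every facility, yet the analysis section mentions neither. The two-group tests that it names have no place for them, and the regression leaves the adjustment set open.

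Two things are at stake. The first is precision: facilities that check BP often before the intervention are likely to do so afterwards, and that part of the between-facility variation can be removed at no cost in data. The second is pre-specification: an open list of confounders does not fix the adjusted treatment estimate in advance.

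A lesser matter is that section 3.3.6 promises twelve intervention facilities, while the procedure it describes does not secure that number.

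**Working it through.** **Inputs from section 3.3.5.** The proportions are 17% and 34%. The test is a "2-sided test with 80% power at a 5% significant level". The clustering inputs are "cluster sizes of 20 adolescents and an intra-cluster correlation coefficient (ICC) of 0.05". The result is that "two groups of ten (10) health facilities will be needed at the minimum", raised to 12 per arm.

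**Step 1: reproduce the plan's figure.**
- Design effect: 1 + (20 − 1) × 0.05 = 1.95.
- Unpooled formula: n = (1.960 + 0.842)² × (0.17 × 0.83 + 0.34 × 0.66) / 0.17² = 99.3 per arm. Then 99.3 × 1.95 = 193.6, and 193.6 / 20 = 9.68 facilities, rounded up to 10.
- Pooled formula: 103 × 1.95 = 200.9, or 10.04 facilities.

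The stated 10 per arm reproduces, and no baseline adjustment enters it.

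**Step 2: the gain from the baseline term.** Let CAC be the cluster autocorrelation, the correlation between a facility's underlying rates in the two periods. The protocol gives no value, so CAC is an assumption. With m = 20 different adolescents at each time, baseline and follow-up facility proportions correlate as

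r = CAC × m × ICC / [1 + (m − 1) × ICC] = CAC × 1.0 / 1.95 = CAC × 0.513.

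A facility-level analysis of covariance multiplies the variance by 1 − r². The facilities column is 9.68 × (1 − r²). Power is for 12 facilities per arm.

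| CAC (assumed) | r | Variance cut | Facilities per arm for 80% | Power, normal | Power, t on 21 df |
|---|---|---|---|---|---|
| 0 | 0 | 0% | 9.7 | 87.7% | 84.5% |
| 0.5 | 0.256 | 6.6% | 9.0 | 89.8% | 86.8% |
| 0.8 | 0.410 | 16.8% | 8.1 | 92.8% | 90.3% |
| 1.0 | 0.513 | 26.3% | 7.1 | 95.3% | 93.4% |

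**Step 3: the cost in degrees of freedom.** With no covariate, t-based power at 12 per arm on 22 df is 84.6%. One baseline term leaves 21 df (84.5% if it explains nothing). Three terms leave 19 df (84.1%). The loss is small beside the gain at any CAC of 0.5 or more.

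**Step 4: arm balance.** The variance relative to 12:12 is (1/a + 1/b) / (2/12).
- 11:13 gives 1.007, a rise of 0.7%.
- 10:14 gives 1.029, a rise of 2.9%.
- 9:15 gives 1.067, a rise of 6.7%.

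Block size and the number of facilities per type are not stated, so both were assumed, with 10,000 simulated sequences per setting. For strata of 1/8/12/3 or 1/9/11/3 and blocks of 2, 4 or a mix, exactly 12:12 arises in about 38% to 50% of sequences. For strata of 2/8/12/2 and blocks of 2 it always does. In the uneven strata, splits more unequal than 11:13 occurred in 0% to 12% of sequences. A 9:15 split appeared only with mixed block sizes.

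**The case against.** The strongest defence is that section 3.4.2 is silent on these covariates and does not exclude them. Its confounder clause could cover both, and naming model terms is often left to a statistical analysis plan, which is not at hand. This stands against any statement that the trial will not use them. It does not rescue the tests that the protocol does name: a z-test or chi-square test on two proportions has no place for a baseline rate or a stratum.

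Several stronger readings are tempting but not supported:

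- **Confounders picked from the data.** The protocol does not say how they will be identified. All that can be said is that the set is left open.
- **A power shortfall.** The 10 facilities per arm reproduces without adjustment, and the trial plans 12. What is forgone is an efficiency gain, whose size hangs on an autocorrelation outside the documents.
- **The 12:12 split is lost.** It is not guaranteed, which is weaker, and the usual departures cost little. Nor can it be shown that particular strata must be uneven. The site list in section 3.2.6 belongs to the health-worker survey, and the trial's own 24 facilities are not listed.
- **The investigator can foresee later allocations.** Section 3.3.6 provides an independent statistician, facility IDs in place of names, and dummy-coded groups. Prediction would need early allocations to become known, the codes to be broken and the block size to be known.

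**Conclusion.** The point holds as a mismatch between design and stated analysis. The protocol collects a facility-level baseline of its primary outcome and stratifies by facility type, but it names neither as an analysis term, and the tests it states cannot use them.

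At m = 20 and ICC 0.05, the baseline term would reduce variance by about 7% to 26% for an assumed cluster autocorrelation of 0.5 to 1.0, less a small loss of degrees of freedom. The gain would be nil if facility habits did not persist at all. The calculation also assumes equal cluster sizes and the same ICC in both periods. The planned 80% power is not put in doubt by this point.

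The allocation wording is a secondary and minor matter: promising twelve per arm while allocating consecutively in stratified blocks leaves a possible imbalance, costing about 3% or less in variance at 11:13 or 10:14.

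That the named tests also ignore clustering is a separate and larger problem, not the subject here, but the remedy below needs a cluster-aware model in any case.

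**What to change.** **Section 3.4.2.** For the treatment comparison, state a facility-level analysis or another cluster-aware model. Give it two pre-stated covariates: the baseline facility BP-check proportion and facility type, with sparse types collapsed by a rule set in advance. Let this replace open-ended confounder selection for the treatment effect.

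For BP and the cardio-ankle vascular index, add the adolescent's own baseline value if the same adolescents are measured twice, and otherwise the facility baseline mean. The protocol should say which applies: section 3.3.4 reads as one sample of 20 for both assessments, while section 3.3.9 (b) can be read as a sample at each time.

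**Section 3.3.6.** Reconcile the consecutive allocation with the promised twelve per arm. Because allocation is withheld until baseline is complete, all 24 facilities can be allocated in one stratified 12:12 step at that point. Constraining that randomisation on the baseline rate as well is optional.

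**Cost.** Wording in two sections and no new data. Facilities recruited early would wait until baseline is finished everywhere.
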